### Study settings

To ensure the generalizability of the results of this study, we planned to enroll patients from several facilities that are representative of typical TB facilities in Uganda. Most patients with tuberculosis [37, 38] are treated at low-level public facilities but a significant burden also exists in urban settings [37, 38]. Therefore, we selected both public and rural TB treatment facilities. Kisenyi Health Center, the first study site, is a large public health center situated within the oldest slum in Kampala which is home to over 23,000 people vulnerable to TB. As a result, the facility receives about 25 new TB patients per month. In addition, Kiryandongo is a rural agrarian district hospital that serves 266,000 people, including 50,000 refugees. The hospital registers an average of 9 new TB cases per month. In contrast, Kasangati Health Center IV is a busy peri-urban facility that serves the Kyadondo East in the Wakiso district and attends to approximately 24 new TB cases per month. To expedite participant accrual, two additional facilities were added to the study protocol version 2.0. Bweyogerere and Kawanda Health Centre IIIs are in the Wakiso district and serve a peri-urban population. They treat approximately 12 patients with TB each per month.

At all health facilities [39, 40], patients with at least one of the dangerous symptoms of TB are offered a sputum GeneXpert test while those unable to expectorate are offered alternative diagnostic tests (CXR, TB LAM, sonography, tissue biopsy, CSF analysis, etc.). Patients with sputum-positive TB are then tested for rifampicin resistance using the GeneXpert MTB Rif assay [40].

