### The intervention (CFL-TB)

CFL-TB delivers once-daily adherence reminders, pre-appointment reminders, and targeted educative behavior change messages and allows patients to report symptoms to health care workers (HCWs) remotely. As advised by Iribarren et al., participants will decide their preferred language and the timing and frequency of reminders and will ensure that the content is culturally sensitive [44]. The software also delivers calls to registered care providers (buddies) of patients to facilitate daily observed therapy (DOTS), in line with the World Health Organization and Ministry of Health guidelines [14, 40]*.* In Uganda, daily reminders are generally preferred by patients over weekly reminders [8]. To increase adherence to the intervention, if the first call is not answered, the system will make two additional calls, 15 min apart. The study staff will also interview participants in the intervention arm to determine whether they are experiencing any problems. Health care workers enroll patients in the system, monitor the delivery message delivery of messages, and provide ongoing technical support, such as setting personal identification numbers (PINs) and swapping the registered telephone numbers. In contrast, participants are responsible for making and receiving calls. We will synchronize appointment reminders with scheduled appointments, and the software will initiate a call before and on the day of the clinic review. Participants select their preferred time to receive the reminder calls and set their PIN. The system offers short educational messages to increase knowledge about TB/HIV and general health [40]. The CFL-TB software is interoperable with other health information systems used in Uganda, including DHIS2, a web-based database for health reporting.

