### Participant follow-up, procedures, and timelines

Participant follow-up before six months, the total study duration is 24 months, and participants will have evaluations at baseline and months 2, 5, and 6, consistent with the Ministry of Health visit scheduling for patients with TB (Table 1). At each visit, the participants will be given their future appointment dates.

**Table 1 Tab1:** Study timelines and procedures

Study procedures	Study procedure completed							
Month	0	0	2	2	5	5	6	6
Study arm	I	C	I	C	I	C	I	C
Screening	**√**	**√**						
Informed consent	**√**	**√**						
Physical evaluations and interviews	**√**	**√**	**√**	**√**	**√**	**√**	**√**	**√**
Demographic and socio-economic questionnaire	**√**	**√**	**√**	**√**	**√**	**√**	**√**	**√**
Sputum GeneXpert^*^	**√**	**√**			**√**	**√**	**√**	**√**
Drug culture and susceptibility tests^β^	**√**^β^	**√**^β^	**√**^β^	**√**^β^	**√**	**√**	**√**^β^	**√**^β^
Cost-effectiveness questionnaire	**√**	**√**	**√**	**√**	**√**	**√**	**√**	**√**
Qualitative assessment	**√**	**√**	**√**	**√**			**√**	**√**

Note: I-Intervention arm, C-control arm

^*^Additional tests to ascertain sputum conversion may be added at the discretion of the investigator.

^β^Drug susceptibility testing will be done in-line with national TB guidelines. Sputum cultures may be done at 2 months to ascertain sputum conversion and sputum for genotyping TB stored.

**√** indicates procedure completed at the indicated timeline

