### Data collection

At baseline, the staff will obtain sociodemographic data (age, sex, marital status, level of education, employment status, income, transport costs, distance from the facility) and data on TB infection (method of diagnosis, site of infection, and rifampicin resistance at baseline). Prospectively, data will be obtained on adherence, symptoms, sputum tests, missed appointments, and clinic visits (Table 1). Participants will also be interviewed on phone call costs, hospitalization, and over-the-counter treatments. At baseline, we will interview patients (qualitative data) on their anticipated challenges in the use of IVRT and anticipated benefits and challenges. At months 2 and 6, qualitative data will be collected on acceptability and experience with the digital intervention. We will determine the sputum conversion rate at 2 months and cure at 6 months. Chest radiographs will be used to determine the cure for patients with clinical TB. TB cards and treatment registers will be reviewed for death, adherence, and date of patient visits. We will use micro-costing to obtain data on the direct and indirect costs.

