### Trial endpoints

The primary endpoint is treatment success (at 6 months): treatment success is a composite outcome, comprising treatment completion and cure in patients with clinically and bacteriologically diagnosed TB, respectively. It is a robust and agreed indicator of treatment success in TB programs. In patients with bacteriologically diagnosed TB, cure is defined as having a negative sputum test in the last month of treatment and on at least one previous occasion [47]. For clinically diagnosed patients, completion entails 6 months of therapy. The denominator for each arm will be the number of patients enrolled. At the same time, the numerator is the sum of bacteriologically and clinically diagnosed patients with cure or treatment completion, respectively.

This RCT also has several secondary endpoints. First, we will determine the TB cure rates in patients with microbiologically diagnosed TB. Second, we will determine treatment completion for patients clinically diagnosed with TB in the two arms: Third, retention rates will be determined and compared between the study arms. Patients will be deemed to be actively engaged in care if they attend a clinic visit within one month of a scheduled appointment. Additionally, we will compare appointments. We will categorize visits as “early,” if they present before an appointment, “prompt” if they show up within three days after the appointment date, “late” if they present after three days but within 30 days of a scheduled appointment and missed if patients do not show up at all or present after 30 days. Fourth, we will determine the incremental costs per additional DALY averted per percentage point increase in treatment success in the intervention versus the control arm. In addition, we will compare adherence rates at months 2 and 6. Depending on the availability of drug susceptibility tests, we will compare the rates of MDR-TB. To understand the impact of the intervention on the treatment outcomes and the potential for adoption and scaling of the intervention, we will explore the perceptions and experiences of patients and care providers towards the MHI. Finally, we will determine the uptake and adherence to the intervention. We will consider the successful receipt of a reminder as a proxy for the utilization of the technology. Therefore, we will determine the proportion of successful calls in the intervention and control arms.

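### The primary endpoint depends in part on sputum collection: a bacteriologically confirmed patient who completes treatment without two negative sputum tests is a non-success, and visit reminders go to one arm only

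*Protocol article*

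**What the plan says.** The Trial endpoints section defines treatment success at six months as a composite "comprising treatment completion and cure in patients with clinically and bacteriologically diagnosed TB, respectively". For the bacteriologically diagnosed, "cure is defined as having a negative sputum test in the last month of treatment and on at least one previous occasion". For the others, "For clinically diagnosed patients, completion entails 6 months of therapy". The denominator is the number enrolled in each arm, and "the numerator is the sum of bacteriologically and clinically diagnosed patients with cure or treatment completion, respectively". The split by type of diagnosis is thus stated twice.

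Table 1 ticks GeneXpert after baseline at months 5 and 6 only. A separate row for culture and susceptibility testing is ticked at months 2, 5 and 6. The month-2 and month-6 ticks carry a footnote tying susceptibility testing to national guidelines and adding that "Sputum cultures may be done at 2 months to ascertain sputum conversion". The Data collection section, by contrast, says that conversion at two months will be determined.

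In the intervention arm, "the software will initiate a call before and on the day of the clinic review". Standard care, as described in the section on the control arm, has no such calls. Better appointment keeping is one of the secondary objectives.

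On a related matter, the Data collection section says: "Chest radiographs will be used to determine the cure for patients with clinical TB". The endpoint definition for these patients does not use a radiograph, and Table 1 lists none.

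**The concern.** A confirmed patient can take all six months of treatment, recover, and still be counted with those who died, defaulted or stayed positive, simply because a sputum result is absent. Some loss of this kind would lower the success rate in both arms without separating them.

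The comparison itself is at risk because samples are collected at visits, and prompting people to attend visits is part of the intervention. If completers in the intervention arm give samples more often, more of them meet the cure rule even when equal proportions complete and recover. The trial would then report better treatment outcomes when part of the difference is better documentation.

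Nothing else in the article separates the two. The completion endpoint covers clinically diagnosed patients only, and the cure endpoint carries the same dependence. The Sensitivity analysis section stratifies by tool use, HIV status, TB type and gender, none of which addresses completers without sputum.

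**Working it through.** **Classification.** This follows from the text without arithmetic. A confirmed patient who completes six months of therapy is in the denominator. Completion enters the numerator only for clinically diagnosed patients. Without a last-month negative and an earlier negative, the confirmed completer is not a cure and so not a success.

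**Number per arm.** The article states 137 per arm (274 in total) for a 15-point difference, power 0.8, alpha 0.05 and 11.8% loss to follow-up. It gives no control rate, so the figure cannot be rebuilt from its inputs alone. An assumed 70% versus 85% needs 121 per arm, and 121/(1 − 0.118) = 137.2, rounded up to 138. That is close to the stated 137, which is used below.

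**Size of a spurious difference.** Inputs that the article does not give, and that are therefore assumptions:
- b = 0.70, the share bacteriologically confirmed
- c = 0.85, the proportion completing and recovering, equal in both arms
- s, the probability that a confirmed completer has the sputum results the rule needs, all of them negative when obtained

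Observed success = c × (1 − b + b × s). The spurious difference is therefore c × b × (s_int − s_ctl) = 0.595 × (s_int − s_ctl).

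If two independent samples are needed, s is the square of the per-visit capture. If only one is limiting (for example because an earlier negative is already on file, or because the same patients miss both visits), s is the per-visit capture itself. The last column is the chance of p<0.05 in a two-sided two-proportion z test with 137 per arm.

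| Per-visit capture, control vs intervention | Samples limiting | s, control vs intervention | Observed success | Difference | Chance of p<0.05 |
|---|---|---|---|---|---|
| 85% vs 85% | two | 0.7225 vs 0.7225 | 68.5% vs 68.5% | 0 | 5% |
| 85% vs 88% | one | 0.85 vs 0.88 | 76.1% vs 77.9% | 1.8 points | 6% |
| 85% vs 88% | two | 0.7225 vs 0.7744 | 68.5% vs 71.6% | 3.1 points | 9% |
| 85% vs 92% | one | 0.85 vs 0.92 | 76.1% vs 80.2% | 4.2 points | 13% |
| 85% vs 92% | two | 0.7225 vs 0.8464 | 68.5% vs 75.9% | 7.4 points | 28% |

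Varying b from 0.5 to 0.8 and c from 0.80 to 0.85 in the last row gives 5.0 to 8.4 points and 15% to 33%. That range holds the capture gap fixed, and the capture gap is what drives the result. The table, which varies it, is the better guide.

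**Understatement.** With equal capture of 85% per visit and two samples needed, a true 85% is recorded as 68.5% in both arms.

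**The case against.** The strongest reply is that the obvious reasons for missing sputum do not differ by arm. A reminder call does not help a patient who cannot produce sputum or whose disease is extrapulmonary, nor one reviewed by phone. Only missed attendance can differ, and the patients at issue have completed six months of therapy with monthly reviews, with staff tracing missed visits in both arms. This stands: the gap among completers may be small, and nothing in the article establishes 7 points. Part of any gain in attendance is also real retention, which is the intended route to success.

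Nor does the article show that both late samples are always needed. Table 1 ticks culture at months 2, 5 and 6, its notes allow extra tests for conversion, and any earlier negative satisfies the rule. That is why the one-sample rows belong in the table.

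Two stronger readings are tempting and not supported. A reader might infer that the endpoint simply measures sputum collection. It does not: death, default and positive sputum also decide it, and clinically diagnosed patients need no sputum. A reader might also infer that the best responders are systematically lost because they stop producing sputum, or because phone reviews replace the late samples. The article says neither. Its remark that "those unable to expectorate are offered alternative diagnostic tests" concerns diagnosis, not month 6, and the provision for phone reviews does not mention sputum.

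None of this touches the classification rule, or the fact that the prompts go to one arm.

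**Conclusion.** The concern holds in a limited form. As written, a confirmed completer without the required negatives is a non-success, success is understated in both arms, and any arm difference in sample capture among completers passes into the primary result. That reminders raise capture is an intended effect, not a demonstrated one.

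The size cannot be fixed from the article. Under the stated assumptions it runs from nothing with equal capture, through about 3 points for a 3-point per-visit gap with two samples needed, to between 4.2 and 7.4 points for a 7-point gap. Against a target of 15 points, the upper end would matter to how the result is read. The lower end would not. The article plans no report of capture by arm, so a reader of the results could not tell which applies.

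**What to change.** In the Trial endpoints section, before any unblinded comparison, define success in bacteriologically diagnosed patients as cure, or completion of treatment with no positive sputum at month 5 or later. Keep the two-negative cure rule as the existing secondary endpoint, and also run it as a sensitivity analysis of the primary endpoint. Report month-5 and month-6 sputum availability by arm.

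No new visits or tests are needed, but this is more than a change of wording. The trial is open-label and, by the Trial status section, 123 of 274 participants were already enrolled. If the sponsor keeps the published primary endpoint for that reason, the cure-or-completion analysis should be a prespecified key sensitivity analysis.

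The change has a cost in the opposite direction. Completers without sputum may be unrecognised failures, and an arm with less testing would have fewer failures detected. The cure-only analysis and the report of sputum availability would show how much this matters.

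Separately, the statement on chest radiographs under Data collection, the six-months-of-therapy rule under Trial endpoints and the absence of a radiograph from Table 1 must be reconciled, so that it is clear what decides success in clinically diagnosed patients.

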### Participant withdrawal and post-trial care

Participants can be withdrawn from the RCT at their request, following death or disengagement from care. Participants may also be withdrawn at the discretion of the investigator for safety concerns. If the subject withdraws from the RCT, the study staff will not perform further evaluations, and data collection will cease. The RCT will retain data collected before withdrawal unless the participant requests otherwise. Study staff will track participants who miss visits. If a participant does not attend for two consecutive months, they will be considered lost to follow-up (attrition). All withdrawn participants will be linked to the standard of care. Participants with cured TB will be exited from care while those with no evidence of cure will be linked to tertiary TB services at their treatment facilities. At the end of the RCT, participants will have their treatment details updated in the TB register and are discharged from care.

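### A clinically diagnosed participant counts as a treatment success on 6 months of therapy alone, even if a scheduled month-5 or month-6 sputum test is positive

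*Protocol article*

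**What the plan says.** All places are in the protocol article.

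- **Trial endpoints** gives the structure of the primary endpoint: "treatment success is a composite outcome, comprising treatment completion and cure in patients with clinically and bacteriologically diagnosed TB, respectively".
- For bacteriologically diagnosed participants, "cure is defined as having a negative sputum test in the last month of treatment and on at least one previous occasion".
- For the others: "For clinically diagnosed patients, completion entails 6 months of therapy".
- On counting, "the numerator is the sum of bacteriologically and clinically diagnosed patients with cure or treatment completion, respectively", and "The denominator for each arm will be the number of patients enrolled".
- **Participant follow-up, procedures, and timelines, Table 1** ticks GeneXpert at months 0, 5 and 6 for both arms, with no limit by type of diagnosis. Culture and susceptibility testing is ticked at month 5; at the other visits it carries a footnote tying it to national guidelines. The footnotes add "Sputum cultures may be done at 2 months to ascertain sputum conversion" and "Additional tests to ascertain sputum conversion may be added at the discretion of the investigator".
- **Data collection** assigns chest radiographs the job of establishing cure in clinical TB.
- **Analysis of endpoints, Table 2** lists the proportion with rifampicin-resistant TB as a separate outcome.
- **Participant withdrawal and post-trial care** says that "those with no evidence of cure will be linked to tertiary TB services at their treatment facilities".

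**The concern.** The trial plans to collect sputum results at the end of treatment from everyone, but the success rule for the clinically diagnosed group does not use them. A participant in that group who takes 6 months of therapy and is sputum-positive at month 5 or 6 enters the numerator of the primary endpoint. If the isolate is rifampicin-resistant, the same person is counted both as a treatment success and as a drug-resistance case.

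The secondary endpoint of completion in clinically diagnosed participants uses the same rule and has the same problem. Any benefit of the intervention that comes through fewer bacteriological failures in this group cannot show in either endpoint.

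The radiograph sentence adds an inconsistency. One section says that cure in clinical TB will be determined, and by what means. The endpoint section gives that group no cure criterion.

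**Working it through.** **Step 1. Apply the written rule to every sputum pattern.** Take month 2 as negative, positive or not done (it is optional), month 5 as negative or positive, and month 6 as negative or positive. That gives 3 × 2 × 2 = 12 patterns. Assume 6 months of therapy were taken.

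| Group | Pattern | Patterns | Scored as success |
|---|---|---|---|
| Bacteriologically diagnosed | month 6 positive | 6 | 0 |
| Bacteriologically diagnosed | month 5 negative, month 6 negative | 3 | 3 |
| Bacteriologically diagnosed | month 5 positive, month 6 negative | 3 | 1 (only with a month-2 negative) |
| Clinically diagnosed | any | 12 | 12 |

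Among the 12 clinically diagnosed patterns, 3 × 3 = 9 contain a positive at month 5 or month 6, and all 9 are successes.

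**Step 2. Size.** The article does not give the clinically diagnosed share *c* or the proportion *q* of that group who are positive at month 5 or 6. Both are assumed here: *c* = 0.10 to 0.40 and *q* = 0.01 to 0.05. All late-positive participants are taken to complete therapy and to give sputum. The arm size of 137 is from Sample size determination.

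Misclassified per arm = 137 × *c* × *q*:
- Lowest: 137 × 0.10 × 0.01 = 0.14 participants (0.10 × 0.01 = 0.1 percentage points).
- Middle: 137 × 0.20 × 0.02 = 0.55 participants (0.4 points).
- Highest: 137 × 0.40 × 0.05 = 2.74 participants (2.0 points).

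The planned 15-point difference corresponds to 0.15 × 137 = 20.6 participants per arm.

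**Step 3. Effect on the comparison.** If *q* is equal in the two arms, both success proportions rise by the same amount and the risk difference hardly moves. Only a difference in *q* is hidden. At the extreme of the assumed ranges (*c* = 0.40, *q* = 0.05 in control and 0.01 in intervention), the hidden difference is 0.40 × (0.05 − 0.01) = 1.6 points.

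**Step 4. Completion endpoint in the clinically diagnosed group.** Here the overstatement is *q* itself, that is 1 to 5 points on the same assumption.

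**The case against.** A reader might infer that no positive sputum can ever count against success, so that anyone still positive at the end is scored as a success. The article does not support that. A bacteriologically diagnosed participant needs a negative test in the last month plus an earlier one, and only cure puts that participant in the numerator. A lone positive last-month result is therefore already a non-success, and a month-5 positive also blocks cure unless another earlier negative exists. The exceptions for this group need an optional month-2 culture, a repeat test or discordant assays at one visit. How to settle discordant assays is detail that an article can leave to the full protocol.

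Three further objections have weight.

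- **Many clinically diagnosed participants may give no sputum.** Study settings says that those unable to expectorate are offered other tests. The true number affected may lie near the low end of the range, or below it.
- **The referral of participants without evidence of cure concerns care after the trial, not scoring.** It does not contradict the endpoint, and this point does not rest on it.
- **A veto by positive sputum makes scoring depend on who is tested.** The trial is open-label and the intervention aims to raise attendance, so the better-attending arm could have more failures found. This limits how the remedy should be written.

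None of this removes the central point. The article states the completion rule, the numerator and the denominator in full, and that stated rule misclassifies a participant with a positive scheduled test. This is not detail left to another document.

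**Conclusion.** The point holds for clinically diagnosed participants only. Their success rule has no bacteriological condition, although the tests that could supply one are scheduled. The Data collection section's use of radiographs for cure in clinical TB also does not fit the endpoint definition, and the two must be reconciled.

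For bacteriologically diagnosed participants the remaining issue is lesser: a month-5 positive lying between an optional month-2 negative and a month-6 negative still scores as cured.

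The effect is about 0.1 to 2.7 participants per arm of 137, or 0.1 to 2.0 points. This rests on assumed values for the clinically diagnosed share (10-40%) and late positivity (1-5%), with full completion and testing among those who are positive. It is small against 15 points. The error raises the success proportion within each arm, but no bias between arms is shown. The reason to correct it is that the primary endpoint should not count a participant with positive end-of-treatment sputum as a success.

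**What to change.** In Trial endpoints:

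1. Define completion for clinically diagnosed participants as 6 months of therapy with no bacteriological evidence of failure on the scheduled month-5 and month-6 tests. Use only the scheduled tests for scoring, not extra ones ordered at the investigator's discretion.
2. Score a participant found to have rifampicin-resistant TB during follow-up as a non-success.
3. Reconcile the radiograph statement in Data collection with the endpoint: either give radiographs a stated role in scoring or say that they have none.
4. As a lesser matter, state how a month-5 positive between two negatives is scored in bacteriologically diagnosed participants.
5. Report by arm how many clinically diagnosed participants had a month-5 or month-6 sputum result, because a positive can be found only in those tested.

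**Cost.** No new tests are needed for the change in the completion rule. The success proportion will be slightly lower, and scoring in this group will depend to some extent on whether sputum is available, which item 5 makes visible. Trial status reports 123 of 274 participants enrolled by May 15, 2021, so the change is a protocol amendment. It would go to the scientific advisory board and then to both approving bodies, and should be settled before outcomes are analysed by arm.

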### Control arm and the standard of TB care in Uganda

The standard of care at all TB treatment centers follows the national TB treatment guidelines [40]. The standard treatment duration is 6 months, except for patients with TB meningitis and osteoarticular TB who require 12 months of treatment. The standard regimen and duration of treatment for patients with drug-susceptible TB are 2 months for isoniazid, ethambutol, rifampicin, and pyrazinamide, followed by four months of rifampicin and isoniazid [34]. Patients are reviewed every 2 weeks for the first month and monthly thereafter. All patients are encouraged to register a close household or community member to directly observe therapy, but this is not enforced. Patients receive health education during clinic visits with messaging on adherence and treatment completion. At treatment initiation, patients are routinely encouraged to adhere to treatment and appointments, but there are often no patient support systems provided to enhance this. Some patients may use other reminder systems of their choice [41] but this has not been described in patients with TB.

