### Analysis of quantitative endpoints

Logistic regression will be used to determine the adjusted odds ratio for TB cure and treatment completion in the intervention arm versus control arms. We will also determine the predictors of TB cure overall and in both arms. The final model will adjust for age, sex, bacterial load, HIV status, TB site, and symptoms at baseline. We will also determine and compare attrition in the two study arms using the Cox proportional hazards model. We will compute the crude and adjusted hazard rates of attrition in the intervention and control arms. The log-rank test will be used to test for differences in attrition between the study arms. Tests for the Cox proportional hazard assumption will be done graphically using Schoenfeld residuals. The model will adjust for age, sex, Karnofsky score at baseline, HIV status, transport costs, distance from the health facility, TB site, and socioeconomic covariates.

We will compare the mean adherence rates (proportion of TB medicines taken as evidenced by TB card) at 6 months in the intervention and control arms. We will treat adherence as a continuous covariate and compare the median adherence between the intervention and control arms. To compare appointment keeping, we will use ordinal logistic regression to determine the adjusted odds ratios of missed, late, and prompt visits (early used as a reference group). In the sensitivity analysis, Poisson regression will be used to compare the number of missed visits and treatment doses in the intervention and control arms. The models will adjust for age, sex, employment, distance from the health facility, and HIV status. We will use chi-square to compare the proportions of patients with MDR-TB between the two study arms. Additionally, logistic regression will be used to determine the crude and adjusted odds ratios of MDR-TB in the intervention and control arms. Finally, as a proxy for the uptake of intervention and fidelity, we will determine the proportions of successful and dropped and received calls at three different (2, 4, and 6 months) to determine patient exposure and acceptance of the intervention through the study treatment period.

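### The 30-day late window reaches or passes the next clinic appointment, so a skipped visit followed by timely attendance can be scored late instead of missed

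*Protocol article*

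**What the plan says.** All references are to the protocol article.

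- **Trial endpoints** sets four categories. Early means before the appointment. Prompt applies "if they show up within three days after the appointment date". The other two, late and missed, are defined together as follows: "if they present after three days but within 30 days of a scheduled appointment and missed if patients do not show up at all". Attendance beyond day 30 also counts as missed.
- **Control arm and the standard of TB care in Uganda** gives the routine calendar: "Patients are reviewed every 2 weeks for the first month and monthly thereafter".
- **Participant follow-up, procedures, and timelines** gives a sparser one: "participants will have evaluations at baseline and months 2, 5, and 6, consistent with the Ministry of Health visit scheduling for patients with TB". It adds that future dates are handed out at each visit.
- **Analysis of quantitative endpoints** puts the categories into an ordinal logistic model. As a sensitivity analysis, "Poisson regression will be used to compare the number of missed visits and treatment doses in the intervention and control arms".

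The article does not say which of the two calendars defines a scheduled appointment for this endpoint.

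**The concern.** A window for late attendance works only if it closes before the next appointment opens. Otherwise one attendance can satisfy two appointments: late for the one skipped and prompt for the one kept. The skipped visit then also fits the no-show clause, so the categories are no longer mutually exclusive.

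Appointment reminders are a core part of the intervention, and adherence to clinic appointments is a listed secondary objective. If some skipped visits are recorded in a milder category, part of any reduction in skipping moves out of the missed count. The score also depends partly on the length of the month, which has nothing to do with the patient's behaviour.

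**Working it through.** There is no stated figure to reproduce, because this is a classification rule. The check applies the article's cut-offs to its own calendars.

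**Rule.** Let L be the days from a scheduled appointment to the next attendance. L < 0 is early, 0 to 3 prompt, more than 3 and up to 30 late, and more than 30 (or never) missed.

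**Calendar.** Routine reviews are taken as days 14 and 28, then five monthly visits, seven in all. The article does not define a month in days, so 28, 30 and 31 are all tried (an assumption).

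**Test 1: skip one visit and attend the next on its due date.** L equals the gap between the two appointments.

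| Skipped visit | 28-day month | 30-day month | 31-day month |
|---|---|---|---|
| Week 2 | 14, late | 14, late | 14, late |
| Week 4 and the next four monthly visits | 28, late | 30, late | 31, missed |
| Last visit | none follows, missed | missed | missed |
| Scored late | 6 of 7 | 6 of 7 | 1 of 7 |

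**Test 2: calendar months.** The gap between the same date in successive months is the length of the first month. Seven of the twelve months have 31 days, so about 5/12 = 42% of gaps are 30 days or less. Enumerating start dates over two years gives the same 42%. Identical behaviour is therefore late in roughly four monthly gaps out of ten and missed in the rest.

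**Test 3: next attendance not exactly on time.**
- 14-day gap: 7 days late gives L = 21, still late.
- 28-day gap: 1 day late gives 29, late; 3 days late gives 31, missed.
- 30-day gap: 1 day late gives 31, missed.
- 31-day gap: 3 days early gives 28, late.

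**Test 4: repeated skipping.** On 28-day months, a patient who attends only days 28, 84, 140 and 168 skips three appointments (days 14, 56 and 112). The lags are 14, 28 and 28 days, so none is scored missed. Two monthly skips in a row give about 60 days for the first, which is missed.

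**Test 5: study-evaluation calendar (months 2, 5 and 6).** Skipping month 2 gives 84 to 93 days, missed. Skipping month 5 gives 28 to 31 days, late or missed. Skipping month 6 is missed.

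**The case against.** The strongest reply is that nothing in Trial endpoints says one attendance may serve two appointments. On an ordinary reading, a patient who never came for the week-2 visit did not show up for it, and it is missed. If the next date is fixed only when the patient returns, there is no intervening appointment and late is coherent. If the endpoint uses the study evaluations, only month 5 is affected. Thirty days also matches the section's own one-month rule for engagement in care. Finally, a rule linking attendances to appointments may sit in the full protocol, a supplementary file that is not shown here.

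Much of this stands. The lack of a linking rule in an article is not itself a fault, and the size of the problem depends on the calendar. What remains is a cut-off that the article does state. Set against the routine calendar it also states, that cut-off makes the late and no-show clauses both apply to the same skipped visit. The text on handing out future dates does not say that they are set only on return.

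A reader might infer that almost no visit can be scored missed, or that the endpoint cannot register skipping. The document does not support either. Missed still arises for the final visit, consecutive monthly skips, disengagement, on-time return after a 31-day gap, any return after day 30, and the month-2 study visit. The ordinal model also still ranks late below prompt, so a skip scored late is not erased.

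**Conclusion.** The point holds, conditional on scheduled dates following the routine clinic calendar. A singly skipped visit followed by timely attendance can then be scored late: always for week 2, and for monthly visits only when the next attendance falls within 30 days. The share of single skips affected runs from 1 of 7 to 6 of 7, depending on how a month is counted.

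The consequence is a blurred boundary between late and missed in the ordinal model and too low a missed count in the Poisson sensitivity analysis. The same rule applies in both arms. How much of a treatment effect would be lost cannot be computed, because the article gives no skipping rates. This is a secondary endpoint, and treatment success is untouched. The overlap itself is certain for the two-week interval; its practical size is less so.

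**What to change.** In Trial endpoints:

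1. State which appointment calendar the endpoint uses, and reconcile the routine review schedule with the study-evaluation schedule.
2. End the late window at the earlier of day 30 and the day before the next scheduled appointment. That gives days 4 to 13 after a two-weekly appointment, 4 to 27 on a 28-day gap, and 4 to 30 on a 31-day gap.
3. Let each attendance count for one appointment only. Assign it to the most recent scheduled appointment not yet attended whose window is still open; otherwise assign it to the next one as early.
4. Score an appointment with no assigned attendance as missed.

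A nearest-date rule should not be used for step 3. On a 28-day cycle, an attendance 20 days after one appointment is 8 days before the next. Step 2 calls it late for the first, while a nearest-date rule would call it early for the second.

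Under these rules, skipping one visit and attending the next on its due date is missed for every gap length, and the patient in Test 4 records three missed visits instead of none.

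The cost is endpoint wording plus re-deriving the categories from visit dates on the TB cards and registers, which are already to be reviewed. Recorded missed-visit rates will rise in both arms.
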